
### 2.12. Statistical Analysis

The data analysis will be performed by the statisticians independent from the research team, and the blinding will be maintained. The statisticians will be experts affiliated with the Kyung Hee University Medical Research Institute.

#### 2.12.1. Statistical Analysis for AD Symptom and GI Symptom Assessments

The continuous variables, including SCORAD, EASI, DLQI, GSRS, and TDS scores, will be presented as mean ± standard deviations with 95% confidence intervals. In the analysis, if the result values follow the mean distribution, the independent two-sample *t-*test can be used; otherwise, the Mann–Whitney *U* test can be used.

On the other hand, the abdominal examination, BSFS, and AR variables are categorical. These will be expressed as *n* (%), and as mentioned above, these will be analyzed using the chi-square test or Fisher's exact test. Data from the 40 participants in the VA group will be compared with those of the 20 participants in the SA group.

For the 40 participants in the VA group, additional analyses will be conducted. With the primary endpoint being the total SCORAD score, we will first analyze the correlation as a continuous variable through regression analysis. The dependent variables will include GSRS, TDS, BSFS, and AR values, as well as abdominal examination findings, which are indicators of GI symptoms.

In addition, based on the above data, we will explore the cutoff total SCORAD value that can distinguish between high and low responders. The reference value set through this process will be divided into categorical variables to evaluate the association with GI symptoms again. The minimal clinically important difference (MCID) acts as an important cutoff that determines whether a response is clinically useful, meaning 8.7 points in total SCORAD and 8.2 points in objective SCORAD [24]. The MCID value will be used for analysis as a reference cutoff value. The purpose of this study is to identify factors associated with response determination by performing a correlation analysis with the above method.

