## 1. Introduction

Atopic dermatitis (AD) is a relapsing and remitting, inflammatory, chronic skin disease that is characterized by severe itching and eczema [1]. Its prevalence varies widely according to geographic location, but according to an International Study of Asthma and Allergies in Childhood (ISAAC)-based report, it is on the rise worldwide, with a global prevalence of approximately 230 million [1, 2]. Additionally, the factors involved in AD pathophysiology are complex and diverse, and recent focus has mainly been on the hygiene hypothesis, loss-of-function mutations of the FLG-encoding gene, environmental factors, and the gut microbiota-skin axis [3].

However, AD cannot be cured [3]. Therefore, multistep guidelines have been outlined to control symptoms and maintain remission for as long as possible. However, in clinical practice, many patients do not respond properly to existing treatments. Persistent, recurring skin symptoms also exist because of treatment discontinuity. On the other hand, if continuous systemic treatment is administered, concerns about side effects and complications come to the forefront [4]. Therefore, to cope with the limitations of these existing treatments, the potential role of East Asian medicine, including Korean medicine, is being actively studied [5, 6]. A recent paper reported that acupuncture is a safe AD treatment that can be effective at improving itchiness, Eczema Area and Severity Index (EASI) scores, and other global symptoms [6].

Our research team has conducted previous randomized controlled trials (RCTs) addressing AD-related topics [7, 8]. Thirty-eight patients with AD were recruited, divided into two groups, and treated with verum or sham acupuncture twice a week for 4 weeks. In that study, acupuncture was performed on three fixed acupoints (ST36, LI11, and PC6 bilaterally) and two additional points. Additional points were selected on an individualized basis according to the accompanying symptoms, such as ST43 and GB41 for gastric stiffness and tenderness or LI2 and GB31 for diarrhea and constipation. Through this study, we not only confirmed the effectiveness of acupuncture treatment but also highlighted two notable implications. The first was that AD severity and the presence of gastrointestinal (GI) symptoms were positively correlated, and the second was that some patients exhibited clear improvements, but some patients did not.

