### 2.11. Outcome Measures

The study outcomes will be evaluated by an investigator blinded to the treatment assignments. There will be no separation between primary and secondary outcomes since the aim of this study is not to confirm the effectiveness of acupuncture treatment in patients with AD but to discover the response determinants and the mechanism of action of acupuncture treatment for AD, mainly focusing on the gut-brain axis.

Clinical outcomes can be divided into three categories: First, we will assess (1) symptoms of AD (changes in SCARAD, EASI, and Dermatology Life Quality Index [DLQI] assessments). We will also assess (2) GI symptoms (changes in abdominal examination findings, as well as changes in scores according to the Gastrointestinal Symptom Rating Scale (GSRS), Total Dyspepsia Symptom (TDS) scale, Bristol Stool Form Scale (BSFS), and the adequate relief of functional dyspepsia pain and discomfort (AR) assessment). These values will be measured at week 0 (baseline), week 2 (midterm), and week 4 (endpoint).

Finally, since this study aims to explore the mechanism of acupuncture, we will also investigate (3) gut-brain axis indicators. First, the changes in the intensity of blood-oxygen level-dependent (BOLD) signals in the pain and itch matrix, including the thalamus, insula, and cingulate cortex, will be measured using fMRI. Additionally, the functional connectivity between the pain and itch matrix regions will be analyzed. Second, a fecal sample will be taken, and the composition of the gut microbiota in the feces will be analyzed. Blood samples will also be collected and analyzed for TARC and ATX in the serum.

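### The GI-response analyses carry no baseline SCORAD term, so the association at the centre of the study is at risk of confounding by AD severity

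*Protocol article*

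**What the plan says.** Section 2.12.1 (Protocol article) sets out three steps that bear on this point.

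- **Arm comparison.** For the continuous scales, "the independent two-sample *t-*test can be used; otherwise, the Mann–Whitney *U* test can be used". No covariate is named.
- **Regression in the 40 verum patients.** Total SCORAD is the endpoint: "we will first analyze the correlation as a continuous variable through regression analysis". The other variables are listed as follows: "The dependent variables will include GSRS, TDS, BSFS, and AR values, as well as abdominal examination findings". Baseline severity is not among them.
- **Responder split.** A cutoff on total SCORAD is to be explored and the resulting groups related to GI symptoms. The reference cutoffs are absolute: "8.7 points in total SCORAD and 8.2 points in objective SCORAD".

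The Discussion (section 3) adds a comparison of improvement between AD patients with and without GI symptoms across all 60 patients, again without a covariate.

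Three other places matter. The Introduction reports from the earlier trial that "AD severity and the presence of gastrointestinal (GI) symptoms were positively correlated". Section 2.11 has SCORAD measured at weeks 0, 2 and 4, so the baseline value will exist. Section 2.12.2 does name AD severity as a covariate, but only for the fMRI correlation analyses.

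**The concern.** The main aim is to find what determines response to acupuncture, and the lead hypothesis is that GI symptoms do. By the protocol's own account GI symptoms go with more severe AD. Baseline severity is also related to almost any SCORAD outcome. Patients with high scores have more room to fall and regress further towards the mean, so they tend to show larger changes; they also tend to end with higher scores. GI symptoms can therefore correlate with the SCORAD outcome in either form when they have no influence on response at all.

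The absolute 8.7-point cutoff shares the problem, because the chance of reaching it depends on where the patient starts. At stake is whether a reported GI determinant is a GI effect or a severity effect under another name. The planned analyses cannot separate the two.

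**Working it through.** **Inputs.** From the protocol: 40 verum patients, SCORAD at weeks 0 and 4, the sign of the severity-GI correlation, and the 8.7-point reference. Not in the protocol, so assumed:

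- r, the correlation of the GI measure with baseline SCORAD: 0.3 to 0.6
- rho, the correlation of baseline with week-4 SCORAD: 0.5 to 0.7
- k, the ratio of week-4 SD to baseline SD: 1 unless stated

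The plan gives no figure for this analysis, so there is none to reproduce.

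**Step 1: induced correlation.** Let GI status have no effect on the week-4 score once baseline is known. Then

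- corr(improvement, GI) = r(1 − rho·k) / √(1 + k² − 2·rho·k), which for k = 1 is r·√((1 − rho)/2)
- corr(week-4 score, GI) = r·rho

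With r = 0.4, rho = 0.5 and k = 1, the first is 0.4 × √0.25 = 0.20 and the second is 0.4 × 0.5 = 0.20. Both are positive, but they mean opposite things: GI patients improve more on the change scale and finish worse on the week-4 scale.

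**Step 2: false-positive rate.** Simulation with n = 40, a two-sided 5% test, 20,000 runs per scenario, no GI effect given baseline and k = 1:

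| rho | r | GI vs change, unadjusted | GI vs week-4 score, unadjusted | Baseline in model |
|---|---|---|---|---|
| 0.5 | 0.3 | 15% | 15% | 5% |
| 0.5 | 0.4 | 24% | 24% | 5% |
| 0.5 | 0.6 | 48% | 48% | 5% |
| 0.7 | 0.3 | 11% | 26% | 5% |
| 0.7 | 0.4 | 16% | 43% | 5% |
| 0.7 | 0.6 | 31% | 79% | 5% |

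Once baseline is in the model, the GI test is the same for change and for the week-4 score. Section 2.12.1 labels the GI measures as dependent; in a simple linear regression, swapping the two sides leaves the test unchanged.

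**Step 3: responder split.** In the same simulations, with the mean fall set equal to the 8.7-point cutoff (assumed), the share reaching it is 54% to 60% in the upper half of GI scores and 40% to 46% in the lower half, for r 0.3 to 0.6 and rho 0.5 to 0.7. GI status plays no part in this.

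**Step 4: sensitivity.** At r = 0.4, testing GI against change:

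- k = 1.3: induced correlation 0.4 × 0.35/√1.39 = 0.12 (rho 0.5) and 0.4 × 0.09/√0.87 = 0.04 (rho 0.7); false positives 12% and 6%
- k = 0.8: 0.4 × 0.60/√0.84 = 0.26 and 0.4 × 0.44/√0.52 = 0.24; false positives 38% and 34%

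At r = 0.2 and k = 1 the rate is 7% to 9%.

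Adjustment is not perfect when baseline is measured with error. A separate simulation assumed a proportional 30% mean improvement, total SCORAD mean 35 and SD 10, and measurement error SD 5. It gave 8% to 18% unadjusted and 6% to 10% adjusted.

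**Step 5: arm comparison, precision only.** Relative to a change-score t-test, the ANCOVA variance is (1 − rho²)/(2(1 − rho)) = (1 + rho)/2. That is 0.65, 0.75 and 0.85 for assumed rho of 0.3, 0.5 and 0.7. A change-score analysis of 60 patients is then as precise as ANCOVA on 60 × 0.65 = 39 to 60 × 0.85 = 51. Relative to a t-test on week-4 scores the ratio is 1 − rho²: 0.91, 0.75 and 0.51.

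**The case against.** **The article may simply be silent.** It is condensed, its variable list need not be complete, and a full analysis plan could carry the covariate. That stands as a limit: the documents show a risk as written, not that no adjustment will ever be made. It does not dispose of the point. Section 2.12.1 names the variables and says the determinants will be identified by that method, and severity is named as a covariate for fMRI but not here. The variance inflation remark in section 2.12.2 hints at multivariable models, but it falls under the gut-brain analyses and does not mention SCORAD.

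**The direction is not fixed.** A reader might infer that the plan is biased towards its own hypothesis. That needs the outcome to be change or an absolute fall. Section 2.11 lists changes and the Discussion speaks of improvement, but the regression in 2.12.1 names only the total SCORAD score. With the week-4 score the bias runs against the hypothesis.

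**The simulated model may not be the planned one.** It pairs baseline GI measures with SCORAD change. Section 2.12.1 does not say when the GI measures are taken, section 2.11 lists changes in them, and Table 1 shows no baseline AR assessment. This stands; the rates do not describe AR.

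**The size is assumed.** The protocol gives the sign of the correlation but not its size, and gives neither rho nor the SDs. The entry window could weaken r, although the Discussion says the earlier trials used the same SCORAD limits.

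**A tempting illustration fails.** An 8.2-point fall is 82% of the entry floor of 10 (8.2/10) but 20.5% of the ceiling of 40 (8.2/40). Both limits are on objective SCORAD, whereas the determinant endpoint is total SCORAD, which also counts subjective symptoms.

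**The arm comparison is valid.** Randomisation protects it, and the protocol says it is not confirming efficacy. This is accepted: only precision is lost.

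**Conclusion.** The point holds as a risk of confounding in the analyses that serve the main aim. Neither the verum regression, the responder split nor the Discussion's subgroup comparison separates GI status from baseline severity, and the protocol itself reports that the two are correlated.

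Under the stated assumptions (r 0.3 to 0.6, rho 0.5 to 0.7, equal SDs, n = 40, baseline GI against change) the unadjusted false-positive rate is about 11% to 48%, against about 5% adjusted. This is an illustration and not an estimate for this trial: it falls to 6% or rises to 38% at r = 0.4 as the SD ratio goes from 1.3 to 0.8. The rates also do not carry over directly to the 60-patient subgroup comparison.

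A reader might go further and conclude that a positive GI finding would be an artefact, or that the verum-sham comparison is biased. The documents support neither. The first depends on correlations and an outcome definition that are not given; the second is ruled out by randomisation. An exploratory study still has to tell a GI effect from a severity effect, so the label does not remove the need for the change.

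**What to change.** 1. State whether the SCORAD outcome in the determinant analyses is change or the week-4 value, and that GI measures are taken at baseline where available. Report AR separately as a measure taken during treatment, since it has no baseline assessment.
2. Include baseline total SCORAD as a covariate in the verum-group regression, in the responder analysis (both the explored cutoff and the 8.7-point reference) and in the Discussion's comparison by GI status. The protocol names no model for the responder analysis, so one that accepts a covariate must be stated.
3. Secondary, for precision only: compare verum and sham on SCORAD, EASI, DLQI, GSRS and TDS by ANCOVA of the week-4 value on arm and the baseline value of the same scale.

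The cost is wording in the analysis plan. All the baseline values needed are already scheduled, so no extra patients, visits or measurements are required. Because measurement error leaves some residual confounding, any GI finding should be reported as an association adjusted for measured severity.

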#### 2.12.2. Statistical Analysis for Gut-Brain Axis Indicators

Changes in the gut-brain axis indicators before and after acupuncture will be analyzed within and between groups.

*(1) Gut Microbiota Analysis*. The significance of categorical variables will be determined using the nonparametric Mann–Whitney test for two category comparisons or the Kruskal–Wallis test when comparing three or more categories. Multivariate analyses of variance (PERMANOVA, 999 permutations) with the vegan function Adonis will be performed to test whether community composition is significantly different according to the features associated with sequencing data.

*(2) Serum TARC, ATX Analyzing*. The significance of continuous variables will be determined using the independent two-sample *t*-test or the Mann–Whitney *U* test. The variables will be presented as mean ± standard deviation with 95% confidence intervals.

*(3) fMRI Analysis*. (i) Preevaluation for fMRI session: the between-group and AD severity-dependent differences in interoceptive and exteroceptive properties will be analyzed using mixed-model linear regression and analysis of variance (ANOVA), with the subject as a random factor. Interoceptive and exteroceptive outcomes will be correlated with functional brain activities (voxel-wise beta-series from sensory imagination tasks) and subjective itch and pain ratings of the tasks, which will be performed during fMRI scanning using Pearson's correlation analyses with and without covariates (AD severity, group). If nonparametric data in one or both variables were present, Spearman's rank order correlation will be used. (ii) fMRI data: raw fMRI data will be preprocessed with Analysis of Functional NeuroImages (AFNI, https://afni.nimh.nih.gov) including slice time correction, alignment, registration, masking, smoothing using a Gaussian kernel, and scaling. For the resting-state fMRI signals, the seed-based amplitude of low-frequency fluctuations, functional connectivity, and graph theory analyses will be performed. Task-related BOLD signals will be compared as a function of the four different types of imagination tasks described below using general linear model tests.

Additionally, trial-specific estimates for each task will be obtained using beta-series regression and a least-squares model, and then the resulting parameter estimates will be used as input features for multivariate pattern analysis. (iii) Video watching and sensory imagination tasks: all intensity ratings will be correlated with functional brain activity and symptom-related questionnaire scores. The effects of sensory imagination tasks and between-group differences, as well as their interactions on subjective ratings, will be analyzed using mixed-model linear regression and ANOVA. Mediation analysis will be performed to identify the factors that mediate brain responses during sensory imagination tasks.

*(4) Multivariate Analysis of Gut-Brain Axis*. For the multivariate analysis of microbiome data, potential microbiome-phenotype associations will be quantitatively assessed by classification and regression models using random forest (RF) and support vector machine (SVM). On microbial sequencing data, relative abundances of operational taxonomic units (OTUs) or collapsed OTUs into genus or species will be used for the microbiome features. For the multivariate analysis of fMRI time series, trial-specific estimates for each task will be obtained using beta-series regression and a least-squares model, and then the resulting parameter estimates will be used as input features for multivariate pattern analysis. The most important discriminating features and their importance scores will be retrieved by running RF and SVM models for AD discrimination (group identification, prediction of disease severity, etc.). The performances of RF and SVM models will be statistically evaluated using mean-square error, coefficient, accuracy, and area under the curve to find the best prediction model and its parameters.

Multicollinearity will be with variance inflation factor (VIF), which identifies the strengths of the correlations between independent variables. We will either exclude variables with high VIF values from the regression analysis or use high VIF values if they contribute to the model.

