## 2. Methods

### 2.1. Objectives

The primary purpose of the present study is (1) to determine the response determinants of acupuncture treatment and (2) explore the underlying mechanism of acupuncture, mainly focusing on the gut-brain axis.

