#### 2.2.1. Randomized Controlled Trial

The RCT component will include only 60 participants with mild to moderate AD. Forty and twenty participants will be randomly assigned to the verum acupuncture (VA) group and sham acupuncture (SA) groups, respectively. It will be a randomized, assessor- and participant-blinded, sham-controlled trial with a parallel-group design. All trial processes and procedures will be carried out at the Kyung Hee University Korean Medicine Hospital and Korea University Brain Imaging Center (KUBIC) in Seoul, Korea.

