#### 2.2.3. Sample Size Calculation

This is not a confirmative study to evaluate the effectiveness of acupuncture. In our previous study [8], we have already confirmed the effectiveness of acupuncture treatment on patients with mild to moderate AD. The aim of this study is to discover the response determinants and the mechanism of action of acupuncture treatment for AD, mainly focusing on the gut-brain axis. Therefore, to calculate the sample size of this study, we considered a sample size of 18 per group calculated based on the SCORAD (total) score as the primary endpoint in our previous study [8] and a sample size of 12 in another study that had a similar design and explored treatment response determinants [10] as well as allocation of the verum acupuncture (VA) and sham acupuncture (SA) groups at a ratio of 2 : 1 to examine the difference in treatment response according to GI symptoms in the acupuncture treatment group. Considering the aim of the present study and the sample size of these previous studies, under the expert agreement, we calculated the required sample sizes for the AD VA, AD SA, and healthy control groups as 40, 20, and 40, respectively.

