Therefore, in this study, we will confirm the activity of each region and the linkage through fMRI as the main indicator of the gut-brain axis. The difference in brain activity between patients with AD and healthy individuals is actively studied [28, 29], and our study will also investigate changes in activity before and after acupuncture. Additionally, the diversity of the gut microbiota and the dominant strain in AD patients have been discussed [39, 40]. In our study, the gut microbiota of the VA treatment group, the SA treatment group, and healthy controls will be compared. Moreover, as mediators connecting the brain and gut, hematologic indicators, TARC and ATX, will be measured together. Effector/memory CD4+ T cells play an important role in allergic diseases. TARC is produced in the intestinal endothelium and epithelial keratinocytes and is known to play a key role in the development and activation of Th2-type inflammatory mediators as well as inducing T-cell chemotaxis [41]. ATX is known to exhibit high mRNA activity in the brain, adipose tissue, ovaries, and small intestine [42], and it has been shown to cause pruritogenic-mediating activity through an ATX-lysophosphatidic acid signaling process in animal studies [43]. Based on these observations and facts, TARC and ATX will be evaluated as mediators that connect the brain, intestine, and skin. The collection and evaluation of these multifaceted data is an advantage of this study.

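### Section 2.12.2 analyses gut-brain changes within and between groups without saying which contrast supports a claim about acupuncture; reading within-arm significance as evidence would favour verum under the 40:20 split.

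*Protocol article*

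**What the plan says.** Section 2.1 gives the primary purpose two parts; the second is to "explore the underlying mechanism of acupuncture, mainly focusing on the gut-brain axis". Section 2.12.2 sets out how the indicators for that part are analysed, and its first sentence is "Changes in the gut-brain axis indicators before and after acupuncture will be analyzed within and between groups". It does not rank the two kinds of analysis.

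The tests that follow are mostly unpaired. For TARC and ATX: "The significance of continuous variables will be determined using the independent two-sample" t-test or the Mann–Whitney test. For the microbiota: Mann–Whitney, Kruskal–Wallis and PERMANOVA. No paired test is named.

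No other section supplies a ranking. Section 2.11 says "There will be no separation between primary and secondary outcomes". The Discussion says of brain activity that "our study will also investigate changes in activity before and after acupuncture", and that sentence does not mention the sham arm.

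On numbers, section 2.2.1 states: "Forty and twenty participants will be randomly assigned to the verum acupuncture (VA) group and sham acupuncture (SA) groups, respectively". Table 1 schedules fMRI, stool and blood at baseline and at the final assessment for the AD patients, so both randomised arms have before and after values. Table 2 gives healthy controls no post-treatment assessment.

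**The concern.** A statement that acupuncture changes BOLD signal, microbiota, TARC or ATX is causal, and in this design only the randomised VA-SA comparison supports it. A before-after change within one arm also contains regression to the mean, habituation to a repeated scan, attention and the passage of time. Such change is plausible here: the Introduction describes a relapsing and remitting disease, and patients enter on a severity score.

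The 2:1 allocation adds a second problem. The same true change is more likely to reach significance in 40 patients than in 20. A pattern of significant change in VA but not in SA can then appear when both arms changed equally, and it appears more often than the reverse pattern. Because the plan lists both kinds of analysis and designates neither, a report could rest a mechanism claim on that pattern and still be consistent with the text.

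A smaller gap concerns TARC and ATX. The opening sentence of 2.12.2 suggests that changes are compared, but the tests themselves do not say so. The comparison with healthy controls has to use values at a single visit, so the same named tests could be run on either quantity.

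**Working it through.** **Is there a figure to reproduce?** No. The article states no alpha, power or effect size for the mechanism analyses. The group sizes of 40, 20 and 40 in section 2.2.3 are attributed to two previous studies, the 2:1 ratio and expert agreement, without formula inputs.

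**Inputs.** From section 2.2.1: 40 VA and 20 SA patients. Assumed, because not stated: two-sided alpha of 0.05, a paired t-test within each arm, no dropout, and the same true standardised change d (mean change divided by SD of the change) in both arms. Equal d means there is no acupuncture-specific effect.

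**Step 1: power within an arm of n patients.** Degrees of freedom n − 1, noncentrality d√n, critical value c equal to the 97.5% point of t with n − 1 degrees of freedom. Power p(n) is the probability that a noncentral t lies outside ±c.

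**Step 2: discordant patterns.** The arms are independent, so

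- P(VA only) = p(40) × [1 − p(20)]
- P(SA only) = p(20) × [1 − p(40)]

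Example at d = 0.4: VA only 0.694 × (1 − 0.397) = 0.418; SA only 0.397 × (1 − 0.694) = 0.121.

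| d | p(40) | p(20) | VA only | SA only |
|---|---|---|---|---|
| 0 | 0.050 | 0.050 | 0.048 | 0.048 |
| 0.2 | 0.235 | 0.136 | 0.203 | 0.104 |
| 0.3 | 0.457 | 0.247 | 0.344 | 0.134 |
| 0.4 | 0.694 | 0.397 | 0.418 | 0.121 |
| 0.5 | 0.869 | 0.565 | 0.379 | 0.074 |
| 0.6 | 0.959 | 0.721 | 0.268 | 0.030 |
| 0.7 | 0.991 | 0.844 | 0.155 | 0.008 |
| 0.8 | 0.999 | 0.924 | 0.076 | 0.001 |
| 1.0 | 1.000 | 0.989 | 0.011 | 0.000 |

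The VA-only probability is at least 20% for d from about 0.20 to 0.66 and peaks near 42%. These are rates for one indicator.

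**Step 3: what the allocation contributes.** With 30:30 the two discordant patterns are equally likely at every d, each peaking at 25%. The asymmetry toward VA therefore comes from the 2:1 split. With 36:18 (10% dropout, assumed) the VA-only figure is 41% at d = 0.4 and 40% at d = 0.5.

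**Step 4: the randomised contrast on the same data.** Simulation with 40,000 trials at each of d = 0.2, 0.3, 0.5, 0.7 and 0.8, using a two-sample t-test on the changes, rejected in 4.9% to 5.0% of trials. It holds its level whatever the common change.

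**Step 5: its power.** For a true VA-SA difference of δ SD of the change, noncentrality is δ/√(1/40 + 1/20) with 58 degrees of freedom. Power is 43% at δ = 0.5 and 80% at δ = 0.78.

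**The case against.** The strongest objection is that the valid contrast is already planned: changes analysed between groups is the VA-SA comparison. That stands. A reader might infer that the plan relies on within-group tests, or that it will often produce a false verum-only finding. The documents support neither. No paired test is named, nothing says a within-VA result may carry a claim, and the within-group part could be purely descriptive. The probabilities above belong to a way of reading results that the plan permits but does not prescribe. They also depend on the size of a common change that the article does not give; the VA-only pattern is no more frequent than the SA-only one at zero change and is rare at 1.0 SD. A paired t-test is, moreover, only a rough stand-in for PERMANOVA or voxel-wise analysis.

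It can also be said that ranking contrasts is a matter for the statistical analysis plan, which is not shown, and that the trial is exploratory: "This is not a confirmative study to evaluate the effectiveness of acupuncture". Both lower the weight of the point. They do not remove it. The quoted sentence disclaims confirmation of effectiveness, whereas mechanism is part of the stated primary purpose, and an exploratory causal claim still needs the contrast that isolates the treatment. The point is also about something the article does state: two kinds of analysis side by side for one causal question.

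Finally, a rule that mechanism claims rest only on VA-SA differences could be read as barring the mediation analysis and the healthy-control comparisons. That is fair, and the remedy has to be limited accordingly.

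**Conclusion.** The point holds as an ambiguity worth removing. Section 2.12.2 plans both within-group and between-group analysis of change, does not designate the randomised comparison as the basis for a claim about acupuncture, and leaves open whether the TARC and ATX tests use change or final values.

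If within-arm significance were used as evidence, equal change in both arms would look verum-specific in roughly one case in five to two in five per indicator for common changes of about 0.2 to 0.6 SD, and more often than it would look sham-specific. Outside that range the risk is small. This rests on assumed two-sided 5% paired t-tests and assumed change sizes. It does not show that the planned between-group analysis is invalid or that a misleading result is likely.

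**What to change.** Add to section 2.12.2:

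- Any claim that acupuncture changes an indicator rests on the randomised VA-SA comparison.
- For scalar indicators (TARC, ATX, alpha diversity, regional BOLD or connectivity summaries), that comparison uses the final value adjusted for baseline.
- For community composition and voxel-wise data, it uses a group-by-time test.
- Within-group changes are reported as estimates with 95% confidence intervals, and their p-values are not compared between arms.
- Mediation analysis and comparisons with healthy controls remain as planned exploratory analyses.

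The baseline and final values needed are already scheduled in Table 1, so no visit, sample or patient is added. The cost is in inference. Within-VA p-values can no longer support a claim, and the deciding contrast is less powerful than the within-VA test: without baseline adjustment, 43% for a VA-SA difference of 0.5 SD of the change, against 87% for the within-VA test of a 0.5 SD change. The two tests answer different questions, so that loss is the price of attributing the change to acupuncture.
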